### Data collection

All patient data for the study will be recorded in the online case report form (CRF) with reference to the patient study number, in compliance with Good Clinical Practice guidelines. Data will be stored in a secure data platform, managed by an independent data manager. The forms were created by the study coordinator ([name]) and the principal investigator ([name]) and reviewed by the steering committee. Data quality and completeness will be checked by the study monitors, who will be granted access to the online CRF and the hospital (electronic) medical records of the included patients for the duration of their monitoring activities.

*Baseline data (t = 0 months)* will be collected before treatment initiation and include patient demographics, date of ESES diagnosis, onset of ESES, seizure type(s), anti-epileptic drug history, detailed history of psychomotor development and behaviour, estimated age at onset of developmental arrest or regression, impression of global functioning assessed with VAS score (− 5 to 5), and neurological examination. Ancillary investigations related to aetiology will be reassessed or scheduled (if not yet performed) and will include a cerebral MRI (dedicated epilepsy protocol) and genetic tests if no aetiology is known (array CGH, mutation analysis including GRIN2A gene). Metabolic screening and a cerebrospinal fluid tap will be performed if considered indicated.

### Sleep EEG at baseline and after 1, 3, 6, and 18 months

The diagnosis of encephalopathy with ESES will have to be confirmed by whole-night EEG recording prior to randomisation. Depending on the logistics of the participating centres, either sleep-deprived EEGs of at least 1 h or whole-night recordings will be considered adequate for follow-up assessments. Technical requirements for the EEG recordings are specified in an appendix to the study protocol. Clinical neurophysiologists will be blinded to the type of treatment.

For each EEG, the spike wave index (SWI) will be calculated in an epoch of 10 min (600 s) duration, starting 5 min after alpha attenuation or after sleep had clinically commenced. The number of seconds containing epileptiform discharges is divided by the total number of seconds in the epoch (600) and multiplied by 100 to reflect the SWI as a percentage.

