### Outcomes

The co-primary outcome measures at 6 months will be cognitive functioning, assessed with a full neuropsychological assessment (NPA):
Intelligence quotient (IQ), or developmental quotient (DQ), compared to baseline IQ/DQ. Improvement is defined as an increase by 10 IQ/DQ points.Cognitive sum score (as defined below). Improvement is defined as statistically significant when improved by at least 75% of the standard deviation (SD).

Secondary outcome measures at 6 and 18 months will include the following:
Changes in individual absolute test results, and IQ/DQ scores, compared to baseline.Changes in spike wave index (SWI) during non-REM sleep, compared with baseline SWI.Changes in seizure frequency assessed for all reported seizure types combined, with improvement being defined as at least 50% decrease as compared with baseline.Changes in subjective global daily functioning assessed with a visual analogue score (VAS) of − 5 to + 5 as compared with baseline.Safety and tolerability, as assessed by the occurrence of adverse events.Change in inflammatory markers post-treatment as compared to levels prior to treatment.Identification of autoantibodies as potential biomarkers of disease severity (TIQ, presence of developmental regression, arrest, or delay and SWI at baseline) and treatment efficacy.

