### Data collection during follow-up

Epilepsy characteristics and information on neurodevelopment, other medical history, neurological examination, concomitant medications, possible treatment emergent adverse events, and sleep EEGs will be collected 1, 3, 6, and 18 months after start of treatment. Neuropsychological assessments will be repeated only after 6 and 18 months to minimise re-test bias. After 3 months, a brief assessment of cognitive performance is performed by the clinician to detect possible ongoing regression that may warrant a change of treatment. In the corticosteroid treatment group, additional safety and tolerability assessments will include monitoring of blood pressure, glucose, and protein in urine and weight monitoring once weekly plus additionally at any hospital visits (including admissions for methylprednisolone pulses, when applicable). In case of stress, high fever or illness managements in these situations will be left to treating physician and details will be recorded in eCRF.

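### Change in SWI may compare a whole-night baseline EEG with a sleep-deprived follow-up EEG, because no rule shown fixes the follow-up recording type (minor; secondary outcome)

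*Protocol article*

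**What the plan says.** All references are to the Methods of the protocol article.

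- **Before randomisation** (Sleep EEG section): "The diagnosis of encephalopathy with ESES will have to be confirmed by whole-night EEG recording prior to randomisation". No other pre-treatment EEG is described, so baseline SWI presumably comes from this recording. The text does not say so outright.
- **At months 1, 3, 6 and 18** (same section): "either sleep-deprived EEGs of at least 1 h or whole-night recordings will be considered adequate for follow-up assessments". What decides the type is given as "Depending on the logistics of the participating centres".
- **Scoring** (same section): "For each EEG, the spike wave index (SWI) will be calculated in an epoch of 10 min (600 s) duration, starting 5 min after". The reference point that follows there is the onset of sleep, judged from the loss of alpha activity or clinically. One rule therefore covers all recordings. On reading, "Clinical neurophysiologists will be blinded to the type of treatment".
- **Further detail** (same section): "Technical requirements for the EEG recordings are specified in an appendix to the study protocol". That appendix is not part of the article.
- **Outcome** (Outcomes section), among the secondary measures at 6 and 18 months: "Changes in spike wave index (SWI) during non-REM sleep, compared with baseline SWI".
- **Allocation** (Treatment section): 1:1 in blocks, stratified by centre, and open label for families and treating physicians.
- **Analysis** (Statistical analysis section): continuous outcomes are shown as means with 95% confidence intervals and compared primarily by a t test or Mann-Whitney U test.

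**The concern.** A change score is easiest to interpret when both measurements are made under the same conditions. Here the stated rule lets them differ. A child may have natural night sleep at baseline and sleep after deprivation at month 6, and the difference is still reported as change in SWI. Nothing in the text shown keeps the type constant within a child, or the same for both arms within a centre.

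This is not a detail that an article merely left out. The article states the rule, and the rule itself permits comparisons of unlike recordings.

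Two things are at stake, and they differ in weight:

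- **Within-arm change.** If the recording condition affects SWI, the mean change in each arm is shifted in proportion to the share of children followed with sleep-deprived EEGs.
- **Between-arm contrast.** This is the stated SWI objective. A shift common to both arms cancels and leaves only extra noise. Bias needs a mix of types that differs by arm.

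**Working it through.** **The plan's own figure.** The Sample size calculation section states 116 evaluable children for 50% vs 25% (80% power, two-sided 5%), raised to 130 for 10% dropout, and a detectable d of around 0.5 for continuous outcomes. These figures reproduce:

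- The two-proportion formula without continuity correction gives 58 per arm, 116 in total. 116/0.9 = 128.9, so 129 against the stated 130.
- Detectable d = (1.960 + 0.842) × √(2/n), which is 0.52 at 58 per arm and 0.49 at 65 per arm.
- Power for d = 0.5 is 76.8% at 58 per arm and 81.3% at 65.

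None of these figures is in dispute. They give the scale for what follows.

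**Inputs that the documents do not give (assumptions).** The mean shift in SWI due to recording type is s = 5, 10 or 15 points, of either sign. The SD of SWI change is 25 points. There are 58 evaluable children per arm. The share p with a sleep-deprived follow-up EEG is 0.5.

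**1. Within-arm mean change.** Shift = p × s = 0.5 × 5, 10, 15 = 2.5, 5.0, 7.5 points.

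**2. Between-arm contrast, equal mix.** Bias = s × (p₁ − p₂) = s × 0 = 0. The error rate stays at 5% for any s.

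**3. Noise, equal mix.** Added variance as a share of SD² is p(1 − p)s²/SD² = 0.25 × s²/625:

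| s (points) | Added variance | SD of change | Power for d = 0.5, 58 per arm |
|---|---|---|---|
| none | 0% | 25.0 | 76.8% |
| 5 | 1% | 25.1 | 76.4% |
| 10 | 4% | 25.5 | 75.2% |
| 15 | 9% | 26.1 | 73.2% |

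Here d = 0.5 means 12.5 points (half the assumed SD of 25).

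**4. Between-arm contrast, unequal mix (hypothetical).** SE = 25 × √(2/58) = 4.64 points. The false-positive rate is P(|Z + bias/SE| > 1.96):

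| Difference in share between arms | Bias for s = 5, 10, 15 (points) | False-positive rate |
|---|---|---|
| 0 | 0, 0, 0 | 5%, 5%, 5% |
| 25 percentage points | 1.25, 2.5, 3.75 | 5.8%, 8.4%, 12.7% |
| 50 percentage points | 2.5, 5.0, 7.5 | 8.4%, 19.0%, 36.5% |

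The last two rows show only how sensitive the result is to imbalance. Nothing in the documents says that an imbalance of either size will occur.

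**The case against.** The strongest reply has five parts.

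**Rank.** SWI change is one of several secondary outcomes, and the co-primary outcomes are cognitive. A reader might take SWI for the key EEG endpoint. EEG improvement is part of the hypothesis in the Background, but the documents nowhere give SWI change that status.

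**Scoring is standardised.** The epoch is the same 600 seconds for every EEG and readers are blinded. This removes recording length as a cause. It does not equalise the conditions under which the child fell asleep. Whether deprivation or time of day moves SWI, and by how much, is not stated anywhere in the documents.

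**Centre stratification.** The text makes recording type depend on the centre, and allocation is balanced within centre. This stands, and it is why noise is the expected cost for the contrast. It protects fully only if each centre keeps to one type, which the text shown does not require.

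**Admissions.** A reader might infer that the treatment effect itself is confounded: most centres give corticosteroids as monthly intravenous pulses with hospital visits, so overnight EEGs would be easier to arrange in that arm. The documents do not support this as a finding. Centre logistics are the stated determinant, the arm may also receive oral prednisolone, and nothing ties the month-6 EEG to a pulse. The pulses are intended to stop after 6 months, so the argument does not apply at month 18. The route is possible at month 6 but not shown, and error rates of 19% to 37% should not be quoted as a property of this trial.

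**Material not shown.** The EEG appendix may contain a matching rule, and the CRF may already capture the type. A covariate for a secondary outcome is also commonly left to the analysis plan, so its absence from the article is not held against the protocol. The point rests only on the freedom that the main text grants.

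**Conclusion.** The point holds as a minor one, limited to a secondary outcome. The stated rule allows SWI change to be taken between unlike recordings, so within-arm mean change can include a difference in recording condition: 2.5 to 7.5 points if half the children have sleep-deprived follow-up and the shift is 5 to 15 points. The between-arm contrast has no bias from this source when the mix is equal across arms. Its cost is then 1% to 9% more variance, which takes power for d = 0.5 from 76.8% to between 76.4% and 73.2% at 58 per arm. Bias in the contrast remains a conditional risk, because type is not fixed within a centre and treating physicians know the allocation.

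This rests on assumed values for the shift, the SD and the share of sleep-deprived recordings, on baseline SWI coming from the whole-night EEG, and on the unseen appendix not already containing a matching rule.

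**What to change.** 1. In the Sleep EEG section or the EEG appendix, have each centre choose one follow-up recording type in advance and use it for all its children, in both arms, at months 1, 3, 6 and 18. Record the type at each visit.
2. Compare SWI at months 6 and 18 between arms by a model with baseline SWI and centre (the stratification factor) as covariates, in place of a t test on raw change. Once type is fixed per centre, the centre term also absorbs an average shift between types, and with it the added noise in step 3 of the working.
3. Tabulate recording type by arm and visit. Adjust for type only in a sensitivity analysis, because it is determined after randomisation and could itself be affected by the arm.
4. Where within-arm change is reported, state that it includes any change of recording type. Do not restrict it to children whose types match: baseline is always whole-night, so that would drop every child at a centre that uses sleep-deprived follow-up and leave a subset selected by centre.

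The cost is a sentence in the protocol or appendix, one CRF field (retrievable from EEG reports for children already followed) and a changed model for one secondary outcome. No extra EEG is needed. The downside is that centres lose the freedom to vary the type from child to child.

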### Neuropsychological assessment at baseline, after 6 months, and after 18 months

Depending on the age and abilities of the patient, tests will be selected from a fixed battery covering the major domains of cognition (intelligence, language, memory, attention, visuospatial functions, executive functions, as specified in an appendix of the study protocol). Administration and scoring will be conducted according to the test manuals. Individual raw test scores at baseline and at follow-up will be transformed into *z*-scores, based on the mean and SD of standard scores. As a measure of overall cognitive functioning, a cognitive sum score will be calculated, representing the mean *z*-score over the 6 domains. Neuropsychologists will be blinded to treatment.

### Cytokine profiles and autoantibodies at baseline and 8 months after start of treatment (2 months after withdrawal of study steroids, to limit the influence of a possible decrease in levels caused solely by treatment)

A snapshot of around 100 cytokines will be analysed (Luminex, X-map technology) in serum of the study participants, (a) at randomisation and (b) 8 months after start of treatment (2 months after withdrawal of corticosteroids). Screening for autoantibodies will be performed using rat brain immunohistochemistry, optimised for extracellular antigens, like NmDAR, AMPaR, GAD, GABABR, LGI1, and Caspr2 [24]. In addition, all samples will be tested by in-house cell-based assays for anti-NMDAR and anti-GlyR antibodies. Samples with positive staining, but no known antibodies, will be tested by immunocytochemistry using live hippocampal neurons. If positive, immunoprecipitation will be the first step towards antigen discovery. The laboratory analyst is blinded for treatment.

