### Treatment

Patients will be enrolled by their treating physician/study doctor, who has no direct insight in the allocation mechanism of the randomisation module. Treatment is allocated according to an automatic online randomisation module with block randomisation stratified for centre to the two treatment regimens (1:1 ratio). The randomisation module was programmed by a data manager. The patients and treating physicians are not blinded for treatment allocation, as this was considered not feasible with two treatment arms that differ in their prescription form (in most centres, corticosteroids are given as intravenous monthly pulses, whilst clobazam is given as a tablet to be taken daily) and because the two treatments require different monitoring. The neuropsychological assessment and EEG assessment will be performed by personnel blinded for treatment:
Clobazam will be administered orally and increased to a dose of 0.5 mg/kg/day within 2 weeks. If well tolerated, dosage may be increased up to 1.2 mg/kg/day (given once daily, in the evening). Treatment with a dosage of at least 0.5 mg/kg/day will be continued for 6 months and thereafter will be either continued or tapered according to the treating physician’s preference. Clobazam is defined by active substance for this study. It is prescribed as tablets, and brand names include Frisium, Onfi, and Tapclob as well as generic products.Corticosteroids: either intravenous methylprednisolone or oral prednisolone will be used, depending on local experience and preference.Intravenous methylprednisolone will be given as monthly pulses. A dosage of 20 mg/kg will be given over 30 min once a day for 3 consecutive days, every 4 weeks, for a total period of 6 months with the intention to stop thereafter.Oral prednisolone will be administered at an initial dosage of 2 mg/kg/day (not exceeding 60 mg/day) for 1 month, followed in the 2nd through 6th month by a dosage between 1 and 2 mg/kg/day (not exceeding 60 mg/day), according to the treating physician’s judgement. Thereafter, prednisolone will be either continued or tapered according to the treating physician’s preference.

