Treatment will be continued for at least 6 months, unless informed consent is withdrawn, the patient develops intolerable adverse effects, or further cognitive regression occurs, requiring an alternative intervention in the opinion of the treating physician. If cognitive regression is observed to continue after 3 months of treatment, according to the impression of the parents or physician, switching to the other treatment arm is allowed. In patients requiring switching to an alternative treatment, an EEG will be obtained before switching.

Drug adherence to oral treatment (oral clobazam or oral prednisolone) will be optimised and monitored by instructing patients to bring their empty packages of study medication to the hospital at every scheduled visit, together with completed drug intake diaries. In addition, for patients treated with clobazam, plasma levels will be measured in blood samples collected between 1 and 3 months after enrolment and between 3 and 6 months after enrolment. For intravenous methylprednisolone, adherence will be confirmed by recording drug administration at times of hospital admission for the monthly pulses.

Concomitant medication will be allowed as long as the patient fulfils the criteria for inclusion. However, changes in concomitant medications are discouraged during the first 6 months. After assessment of the primary endpoint at 6 months, subsequent treatment strategies will be left to the clinical judgement of the treating physician.

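### The month-8 biomarker sample is described as 2 months after steroid withdrawal, but patients who complete oral prednisolone as the protocol prescribes do not have that interval

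*Protocol article*

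**What the plan says.** The section on cytokine profiles and autoantibodies takes blood at randomisation and again at "8 months after start of treatment (2 months after withdrawal of corticosteroids". Its heading repeats the interval and adds the reason: "2 months after withdrawal of study steroids, to limit the influence of a possible decrease in levels caused solely by treatment". The abstract fixes the second sample by time from treatment initiation alone.

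The Treatment section allows two steroid regimens, chosen by local experience and preference:

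- Intravenous methylprednisolone: a 3-day pulse every 4 weeks, "for a total period of 6 months with the intention to stop thereafter".
- Oral prednisolone: 2 mg/kg/day in the first month, then 1 to 2 mg/kg/day in months 2 through 6. "Thereafter, prednisolone will be either continued or tapered", as the physician prefers.

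On the mix of routes it says only that "in most centres, corticosteroids are given as intravenous monthly pulses".

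The same section says that, if regression continues after 3 months, "switching to the other treatment arm is allowed". After the 6-month assessment, "subsequent treatment strategies will be left to the clinical judgement of the treating physician".

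The Outcomes section lists the endpoint that uses the sample: "Change in inflammatory markers post-treatment as compared to levels prior to treatment". It also lists autoantibodies as possible biomarkers of severity and treatment efficacy.

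**The concern.** The draw is tied to the calendar, while the claimed interval depends on when steroids actually stop. The two coincide only if the last dose falls at or before month 6. For oral prednisolone the protocol lists two courses of action after month 6, and neither is a stop at that point. The description therefore fails for one of the two permitted regimens even when nobody deviates.

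At stake is how a lower marker level at month 8 is read. In a patient still on prednisolone, or recently off it, the fall may partly be a direct drug effect, which is what the interval was meant to limit. A reader who takes the description at face value could credit such a fall to a lasting change in disease activity. Patients who switched to steroids after month 3, or who receive them after month 6 on clinical judgement, may also be exposed at the draw, in either arm.

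**Working it through.** **Inputs.** From the article: draw at month 8; pulses every 4 weeks, 3 days each; steroid course of 6 months; oral dosing through month 6 and then continued or tapered; switching allowed after month 3; 65 patients per arm. Conventions: 1 month = 30.44 days, so month 3 = day 91.3, month 6 = day 182.6 and month 8 = day 243.5; the first pulse starts on day 0.

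**Formula.** Steroid-free interval = day 243.5 − day of last steroid dose, and 0 if still treated at the draw.

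**The plan's own figure.** Last dose at month 6: 243.5 − 182.6 = 60.9 days = 2.0 months. The stated interval reproduces, with no slack for any later dose.

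**Intravenous, stopped as intended.** The article does not fix whether 6 months means 6 or 7 pulses, so both are shown.

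| Pulses | Last dose (day) | Interval |
|---|---|---|
| 6 | 5 × 28 + 2 = 142 | 101.5 days = 3.3 months |
| 7 | 6 × 28 + 2 = 170 | 73.5 days = 2.4 months |

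The stated 2 months is met in both cases.

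**Oral completers.** Continued to the draw: 0. Tapered from month 6 over T weeks: interval = 2 − 7T/30.44 months. The article gives no taper length, so the values of T are assumptions.

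| Taper | Steroid-free at month 8 |
|---|---|
| 2 weeks | 1.5 months |
| 4 weeks | 1.1 months |
| 6 weeks | 0.6 months |
| 8 weeks | 0.2 months |
| 8.7 weeks or more | 0 |

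Only T = 0, an abrupt stop at month 6, gives the full 2 months.

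**Switch to intravenous steroids at month 3 (day 91.3).** Four pulses: last dose on day 91.3 + 3 × 28 + 2 = 177.3, interval 66.2 days = 2.2 months. Five pulses: last dose on day 205.3, interval 38.2 days = 1.3 months. The interval survives only with at most four pulses; a later switch would shorten it. The article gives neither the course length after a switch nor how often switching is expected.

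**Number affected.** The oral share is not stated. Assuming that 10% to 40% of the 65 are oral completers: 0.10 × 65 = 6.5 and 0.40 × 65 = 26, so about 7 to 26 patients.

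**The case against.** The best defence is the wording of the heading, which speaks of study steroids. If that means only the 6-month course, month 8 is 2 months after its end, and later prednisolone is ordinary care in a pragmatic trial. This reading rescues the heading at most. The body of the section says corticosteroids without that qualifier, and prednisolone taken between months 6 and 8 acts on the markers whatever it is called.

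A second defence is that the stated aim is to limit drug influence, not to abolish it, and that 2 months is a nominal figure rather than a pharmacological threshold. That has force. A child tapered over 2 weeks has about 1.5 months off steroids and is in a very different position from one still on treatment, so the count of 7 to 26 includes patients with little residual exposure. The assumed share also has no firm anchor, because the article's remark about intravenous use counts centres and not patients.

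Third, dosing dates and exposure analyses normally belong in the case report form or the analysis plan, and their absence from an article is no fault. That is right, and the point does not rest on it. It rests on a positive statement that the article's own dosing rule contradicts. The section on data collection during follow-up lists concomitant medication at months 1, 3, 6 and 18. Month 8 is not among those visits, so it is worth making sure that steroid status at the draw can be recovered.

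**Conclusion.** The point holds. The 2-month steroid-free interval is right for intravenous patients who stop as intended (2.4 to 3.3 months) and wrong for every oral-prednisolone completer managed as the protocol prescribes (0 to just under 2.0 months). That conclusion needs only the article's own timings.

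The reach is limited and uncertain. The affected patients are probably a minority of the steroid arm; 7 to 26 of 65 is illustrative and depends wholly on the assumed oral share. The split between continued and tapered is unknown, as is any contribution from switching. The consequence is confined to the change in inflammatory markers and the month-8 autoantibody result. The co-primary cognitive outcomes and the pre-treatment samples used as predictors are unaffected. This is a matter to consider and not a threat to the trial's main conclusion.

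**What to change.** Keep the month-8 draw and the comparison by randomised arm.

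1. Amend the cytokine and autoantibody section to say that the 2-month interval applies only to patients whose steroids stopped by month 6.
2. Make the date of the last steroid dose available for each month-8 sample in both arms. Use existing records where they reach: the Treatment section already provides for intake diaries and recorded pulse administrations, and the Statistical analysis section plans to report who stays on allocated treatment throughout the study, which requires treatment status to be known.
3. Add one supportive analysis of marker change in three groups: never exposed to steroids; at least 2 months off; less than 2 months off or still on. Label it non-randomised, do not make the main comparison conditional on it, and report a fall seen only in recently exposed samples as possibly a direct steroid effect.

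The cost is one corrected statement, one date per sample and one extra analysis, with no change to treatment, visits or sample size. The analysis has clear limits: the groups will be small, around 100 cytokines are measured, and exposure follows physician choice after randomisation. It can warn against a misreading but cannot settle cause.
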